### **8.1.4 Recording of Adverse Events and Serious Adverse Events**

From the point of signing the informed consent form (ICF) to the first re-boost (first administration of study treatment), any worsening of an existing or new medical condition must be recorded on the Medical History CRF page. Following administration of study medication up to the Visit 10 (End of Study), any worsening of an existing or new medical condition must be recorded as an AE on the CRF. The Investigator should review all documentation (e.g., hospital progress notes, laboratory, and diagnostic reports) relative to the event being reported. The Investigator will then record all relevant

information regarding an AE/SAE on the appropriate CRF page. The Investigator will evaluate AEs using the following guidelines:

- Description of event (if the event consists of a cluster of signs and symptoms, a diagnosis should be recorded [e.g., flu syndrome] rather than each sign and symptom).
- Onset date and time.
- Stop date and time.
- Intensity should be described according to the Division of AIDS Table for Grading Severity of Adult and Pediatric Adverse Events, Version 1.0 December 2004; Clarification August 2009 (Appendix 15.1) as Mild (Grade 1), Moderate (Grade 2), Severe (Grade 3), or Life threatening (Grade 4). Intensity is defined as one of the following:
  - Mild: transient or mild discomfort; no limitation in activity; no medical intervention/therapy required.
  - Moderate: mild to moderate limitation in activity- some assistance may be needed; no or minimal medical intervention/therapy required.
  - Severe: marked limitation in activity, some assistance usually required; medical intervention/therapy required; hospitalization is possible.
  - Life-threatening: extreme limitation in activity, significant assistance required; significant medical intervention/therapy required; hospitalization or hospice care probable.

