#### **10.6.3.1 Adverse Events**

For presentation, AE verbatim text will be coded into a Medical Dictionary for Regulatory Activities (MedDRA) term, and classified by System Organ Class (SOC) and preferred term. AEs will then be summarized and grouped by SOC and preferred term. Results will be displayed in order of decreasing frequency, both across SOC and within each SOC term. AEs with onset on or after the start of study medication are considered treatment-emergent. AEs reported prior to treatment administration will be reported separately from treatment-emergent AEs.

In addition, summaries will be provided by incidence, severity (mild, moderate, severe), and relationship to study medication (Related, Unrelated). "Possibly Related", "Probably Related" and "Definitely Related" or relationship is missing will be grouped as "Related."

SAEs and AEs leading to discontinuation will be listed.

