**I. Instructions and Clarifications**

Grading Adult and Pediatric AEs

The DAIDS AE Grading Table includes parameters for grading both Adult and Pediatric AEs. When a single set of parameters is not appropriate for grading specific types of AEs for both Adult and Pediatric populations, separate sets of parameters for Adult and/or Pediatric populations (with specified respective age ranges) are given in the Table. If there is no distinction in the Table between Adult and Pediatric values for a type of AE, then the single set of parameters listed is to be used for grading the severity of both Adult and Pediatric events of that type.

**Note:** In the classification of adverse events, the term "**severe**" is not the same as "**serious**." Severity is an indication of the intensity of a specific event (as in mild, moderate, or severe chest pain). The term "**serious**" relates to a participant/event outcome or action criteria, usually associated with events that pose a threat to a participant's life or functioning.

Addenda 1-3 Grading Tables for Microbicide Studies

For protocols involving topical application of products to the female genital tract, male genital area or rectum, strong consideration should be given to using Appendices I-III as the primary grading scales for these areas. The protocol would need to specifically state that one or more of the Appendices would be primary (and thus take precedence over the main Grading Table) for items that are listed in both the Appendix and the main Grading Table.

- Addendum 1 - Female Genital Grading Table for Use in Microbicide Studies - [PDF](#)
- Addendum 2 - Male Genital Grading Table for Use in Microbicide Studies - [PDF](#)
- Addendum 3 - Rectal Grading Table for Use in Microbicide Studies - [PDF](#)

Grade 5

For any AE where the outcome is death, the severity of the AE is classified as Grade 5.

Estimating Severity Grade for Parameters Not Identified in the Table

In order to grade a clinical AE that is not identified in the DAIDS AE grading table, use the category "Estimating Severity Grade" located on Page 3.

Determining Severity Grade for Parameters "Between Grades"

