|-----------------------------------------------------------------------------------------------------------------|---------------------------------------------------------------------------------------------------|-----------------------------------------------------------------------------------------------------------------------------|------------------------------------------------------------------------------------------------------------------------------------------------------------------|----------------------------------------------------------------------------------------------------------------------------------------------------------------------------------------|
| Pruritis associated with injection
See also Skin: Pruritis (itching - no skin lesions)                       | Itching localized to injection site AND Relieved spontaneously or with < 48 hours treatment       | Itching beyond the injection site but not generalized OR Itching localized to injection site requiring ≥ 48 hours treatment | Generalized itching causing inability to perform usual social & functional activities                                                                            | NA                                                                                                                                                                                     |
| SKIN – DERMATOLOGICAL                                                                                    |                                                                                                   |                                                                                                                             |                                                                                                                                                                  |                                                                                                                                                                                        |

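### Adverse event intensity is graded by the DAIDS table and by different restated definitions with no order of precedence, and the planned severity summary names three of the four grades recorded

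*Protocol*

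**What the plan says.** Protocol section 8.1.4 gives two instructions in succession. The first is "Intensity should be described according to the Division of AIDS Table for Grading Severity of Adult and Pediatric Adverse Events" (Appendix 15.1), with intensity recorded "as Mild (Grade 1), Moderate (Grade 2), Severe (Grade 3), or Life threatening (Grade 4"). The next sentence begins "Intensity is defined as one of the following" and sets out four descriptions of its own. Mild is "transient or mild discomfort; no limitation in activity; no medical intervention/therapy required"; Moderate is "mild to moderate limitation in activity- some assistance may be needed; no or minimal medical intervention/therapy required". Severe and Life-threatening continue along the same lines: activity, assistance, treatment and hospitalisation. No sentence ranks the two texts. To separate severity from seriousness, 8.1.4 also gives the example of a stroke with limited disability that may be rated mild.

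Three other places bear on the point:
- Section 4.4.1.1 records injection-site reactions as adverse events on a scale of its own: size bands for swelling or redness, and none, mild, moderate or severe for pain and other local reactions.
- Section 4.4.1.2 grades systemic reactions by the DAIDS table and ties a 24-hour sponsor contact to Grade 3 or 4.
- Section 10.6.3.1 plans adverse event summaries by "severity (mild, moderate, severe") and, separately, lists serious events and events leading to discontinuation.

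**The concern.** The restated descriptions do not paraphrase the DAIDS table. The table's generic row grades by how far symptoms interfere with usual activities and, at the top, with basic self-care. Many specific rows use a measured size, a temperature or a diagnosis. The restated text uses limitation, assistance and treatment. Where the two diverge, the recorded grade depends on which sentence the site follows.

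Safety and tolerability is a stated secondary objective, and section 10.6.3 plans no statistical testing of safety, so the descriptive tables carry that objective. A severity table built from two rules, without a category for the highest recorded grade, is harder to interpret than it should be.

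**Working it through.** The protocol states no figure on this point, so the check sets the texts side by side.

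**Step 1: one event, two texts.** Each event is described only as far as the comparison needs.

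| Event (assumed features) | Appendix 15.1 | Section 8.1.4 |
|---|---|---|
| Adult injection-site erythema over 9 cm; mild discomfort, no limitation, no therapy needed | Grade 2, on size alone | Mild: every element is met |
| Injection-site pain slightly limiting use of the limb | Grade 1, which tolerates minimal limitation | Not Mild, which allows no limitation |
| Stroke with limited disability and a neurological deficit | Grade 4 (acute CNS ischemia row) | May be rated mild, by the section's own example |

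The divergence runs both ways. The restated text gives a lower grade for the erythema and the stroke. It excludes Mild for the pain, where the appendix gives Grade 1.

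**Step 2: the third scale.** Under 4.4.1.1, pain is mild when easily tolerated and moderate when it interferes with usual activities, which is neither of the wordings above. The size bands for redness and swelling stop at 3.5 cm and over, whereas DAIDS Grade 1 for an adult local reaction starts at 5 x 5 cm and Grade 2 lies above 9 cm. The top band therefore contains ungraded, Grade 1 and Grade 2 reactions, and the band alone cannot give the DAIDS grade. The pain scale has no life-threatening category, although the notification sentence in the same section refers to life-threatening reactions.

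**Step 3: grades recorded against grades summarised.**
- Recorded under 8.1.4: mild, moderate, severe, life-threatening = 4.
- Named in 10.6.3.1: mild, moderate, severe = 3.
- Without a category: 4 - 3 = 1, life-threatening (Grade 4).

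**Step 4: what the listings recover.** A Grade 4 event that is serious, or that leads to discontinuation, appears in the 10.6.3.1 listings. One that is neither appears in no summary category and in neither listing. The DAIDS heading for Grade 4 is potentially life-threatening, whereas section 8.1.2 requires that the subject was at risk of death at the time. A Grade 4 event therefore need not be serious on that criterion.

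**Step 5: scale.** Section 10.1 expects about 30 to 40 subjects. If the safety population is of that size, one subject moved between severity categories shifts a percentage by 1/40 = 2.5 to 1/30 = 3.3 points. The protocol gives no expected number of discordant or Grade 4 events, so no total can be derived.

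**The case against.** The case for leaving this alone is that many events grade alike under either text, the study has one arm, no decision rule uses the severity table, and table layout normally belongs in the SAP. Most of that is fair and limits the weight of the point. It does not remove the point: the protocol itself fixes three levels against four recorded, and itself supplies the competing definitions.

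Several stronger readings are tempting, and the documents do not support them.

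- *The 24-hour contact rule is compromised.* Section 4.4.1.2 cites the DAIDS table directly, so its trigger is anchored and is not in conflict.
- *Treated itching or a treated fever of 38.0 °C becomes at least Moderate.* DAIDS Grade 1 itching may be "Relieved spontaneously or with < 48 hours treatment", and a fever of 37.7 to 38.6 °C is Grade 1. But the restated Mild turns on therapy being required, not merely given, and the restated Moderate also asks for some limitation in activity. Without that limitation the records do not clearly meet Moderate.
- *Untreated fatigue that prevents usual activities receives two grades.* It is DAIDS Grade 3 and fails the treatment element of the restated Severe, but that yields no second grade.
- *All Grade 4 and fatal events drop out of the report.* The appendix says "For any AE where the outcome is death, the severity of the AE is classified as Grade 5", and 8.1.4 has no such grade. Deaths are nevertheless captured as a fatal outcome and listed as serious events, and most Grade 4 events would probably be listed too.

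**Conclusion.** The inconsistency is real and limited in size. Section 8.1.4 holds two sets of definitions that give different results for identifiable events, including one of its own examples, and 4.4.1.1 adds a third. Local injection-site reactions are among the most common risks named in section 1.6, so the divergence touches an expected class of event, although that section gives no incidence. One of four recorded grades has no category in the planned severity summary. What is lost is a complete severity table, together with any Grade 4 event that is neither serious nor a cause of discontinuation.

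This rests on reading both 8.1.4 texts as binding, since neither is subordinated, and on reading the three levels in 10.6.3.1 as the full set. No efficacy result is affected. It should be corrected, but it does not undermine the safety evaluation as a whole.

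**What to change.** 1. Name one grading source for all adverse events. The DAIDS table is the smallest edit, because 4.4.1.2 and 8.1.4 already cite it; its generic row covers terms it does not list.
2. In 8.1.4, delete the restated definitions or say that they yield to the table wherever they differ.
3. Reconcile the stroke example in 8.1.4 with the appendix row, or replace it.
4. In 4.4.1.1, state how the local scale relates to the chosen source. The size bands can stay as description, with the grade assigned from the measured size. The mention of life-threatening reactions there must be reconciled with a scale that lacks that category; the notification rule itself is for the sponsor to settle.
5. In 10.6.3.1, have the severity summary cover every grade recorded, including life-threatening, and state whether fatal events are shown as Grade 5 or through the outcome field.

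The cost is text edits in three sections and an added table row. No new assessments are needed.

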### 8.1.5 Follow-up of Adverse Events and Serious Adverse Events

All AEs and SAEs must be followed until they are resolved (return to normal or values before re-boosting) or stabilized, or until they are judged by the Investigator to be no longer clinically significant. Supplemental measurements and/or evaluations may be necessary to fully investigate the nature and/or causality of an AE or SAE. This may include additional laboratory tests, diagnostic procedures, or consultation with other healthcare professionals. If the subject dies, any findings (including histopathology) must be provided to the Sponsor (or designee).

### **8.1.6 Reporting of All Serious Adverse Events and Any Adverse Events Resulting in Study Discontinuation**

The Investigator will promptly report all SAEs to the Sponsor (or designee) within the timeframes specified in [Table 2](#). Prompt notification of SAEs by the Investigator is essential so that the Sponsor can meet its regulatory and ethical obligations for this study.

The Investigator should comply with the applicable local regulatory requirements related to reporting of SAEs to his/her EC.

Any SAE, regardless of expectedness or causality, must be reported by telephone and by faxing (or mailing) the completed SAE Report Form to the Sponsor (or designee) within 24 hours of the Investigator or any other site personnel's knowledge of the event. In addition, any AE resulting in permanent study discontinuation for a subject, even if not serious, must be reported immediately to the Sponsor (or designee). An updated SAE Report Form should be forwarded to the Sponsor (or designee) within 24 hours of receipt of the new/updated information. The Sponsor (or designee) will provide a list of project contacts for SAE receipt, fax numbers, telephone numbers, and mailing addresses for SAE reports.

**Table 2 Serious Adverse Event Reporting Requirements**

|                               | INITIAL REPORTS                                                                               | FOLLOW-UP REPORTS                                                       |
|-------------------------------|------------------------------------------------------------------------------------------------------|--------------------------------------------------------------------------------|
| REPORTING REQUIREMENTS | 24 hours
Telephone and fully completed SAE Report Form to the Sponsor (or designee) | 24 hours
Updated SAE Report Form to the Sponsor (or designee) |

For IMPs, an AE is judged expected if its description agrees in nature, severity, frequency, and specificity with the description of events in the current Investigator's Brochure.

Safety Reports will be prepared according to the Sponsor's policies and forwarded to the Investigator as necessary. The purpose of the Safety Report is to fulfill specific regulatory and Good Clinical Practice (GCP) requirements regarding the product under investigation. When a site receives from the Sponsor (or designee) an initial or follow-up Safety Report or other safety information (e.g., a revised Investigator's Brochure), the Investigator is required to promptly notify his EC according to local guidelines, and maintain the information, as well as the documentation of the EC communication, in the site's study files.

### **8.1.7 Post-study Adverse Events or Serious Adverse Events**

Investigators are not obligated to actively seek AEs or SAEs after termination of the study period. However, the Investigator should promptly notify the Sponsor (or designee) if the Investigator learns

of any SAE or death of a study subject within 30 days after a subject has been discontinued from the study, and such event(s) is (are) reasonably related to the study drug.

Investigators should promptly notify the Sponsor (or designee) if they become aware of a former study participant who is one of the parents of a subsequently conceived child with a congenital anomaly.

## **8.2 Pregnancy Information**

If relevant, a urine pregnancy test will be administered at Visit 2 and Visit 3 before re-boosting. If any female subject becomes pregnant during the study, the Investigator must notify the Sponsor (or designee) by telephone within 24 hours of learning about the pregnancy and report it in the electronic CRF (eCRF). The eCRF must be completed within 14 days. The Investigator must diligently follow the subject until delivery or termination of the pregnancy, providing necessary updated information to the Sponsor (or designee). Any premature termination of the pregnancy will also be reported.

Although pregnancy occurring in a clinical study is not considered to be an AE or SAE, any pregnancy complication or elective termination of a pregnancy for medical reasons will be recorded as an AE or SAE and will be followed as such. A spontaneous abortion is always considered to be an SAE.

## **9 DATA COLLECTION**

### **9.1 Data Collection**

Subject data will be collected on eCRF and will be substantiated by subject date of birth, the subject identification number in the Study CT-BI Vacc-4x 2007/1 study and study number. The eCRF will be completed according to guidelines provided by the Sponsor (or designee) in writing and/or verbally. All required data are to be recorded on the eCRF.

Completed eCRFs will be reviewed by the study monitor in line with eCRF review guidelines for the study to ensure completeness and consistency. Data will be collected using the Aptiv Advantage® system, a web-based electronic data capture technology, which is based on an Oracle® platform. The Sponsor (or designee) will subject all eCRF data to 100% source verification and audit to ensure adequate quality control and assurance of subject data. Any discrepancies found during the eCRF review are to be clarified by the Investigator. This includes eCRF reviews at the site by the Sponsor (or designee), or during quality assurance review of the data.

The Investigator (or designee) must record all required subject data using the previously specified data collection method defined by the Sponsor. An explanation must be documented for any missing data. The Investigator must sign and date a declaration on the eCRF attesting to his/her responsibility for the quality of all data recorded, and that the data represents a complete and accurate record of each subject's participation in the study. Each subject eCRF will be retained by the Investigator on a CD.

## **9.2 Data Processing**

Subject eCRFs will be completed from source documents by designated site staff in line with eCRF completion guidelines. The on-going status of data entry will be reflected in the EDC system and will be accessible to all users based on their access privileges.

Data within the eCRFs will be source data verified (100 %) and the EDC system will be updated to indicate which data items have been verified. In the event that changes are made to the eCRF after verification by the CRA, the CRA will be required to re-verify the data.

The eCRF will be approved by the Investigator after it has been verified and all discrepancies resolved. In the event that changes are made to the eCRF after approval by the Investigator, the eCRF must be re-approved.

The eCRF will be validated through extensive data checking and query processing capabilities within the EDC system. Electronic messaging (discrepancy routing) between users will forward discrepancies within the EDC system from one user group to another depending on the action required at the time. A full audit trail of any changes made to the eCRF will also be stored within the system.

## **10 STATISTICAL METHODS AND PLANNED ANALYSES**

### **10.1 Determination of Sample Size**

Eighty-eight subjects completed the initial study CT-BI Vacc-4x 2007/1 (EudraCT Number 2007-006302-13) immunization regimen with active Vacc-4x and stopped ART at Week 28. It is estimated that approximately 30 to 40 of these subjects will be eligible for this follow-up, re-boosting study.

### **10.2 Randomization Codes**

This is a non-randomized study.

### **10.3 Populations to be Analyzed**

The following populations will be used in the analyses:

**Safety:** All subjects who receive at least one re-boosting immunization will be included within the safety population. All safety analyses will be conducted on the safety population.

**Intention to treat (ITT):** All subjects who receive at least one re-boosting immunization and have any post-baseline efficacy data will be included in the ITT population. Unless otherwise indicated, all efficacy analyses will be conducted on the ITT Population.

**Per protocol (PP):** All ITT subjects who receive two re-boosting immunizations, discontinue ART at Visit 5 (as planned) and who do not incur a major protocol violation that would challenge the validity of their data will be included within the PP population. All efficacy analyses will also be conducted on the PP population.

